**Theme: *(Check all that apply)***

Nutrition  Environmental Health

Emerging and Re-emerging Infectious Diseases  Health Services

Population Dynamics  Child Health

Reproductive Health  Clinical Case Management

Vaccine evaluation  Social and Behavioural Sciences

HIV/AIDS

### Key words: Vitamin A, Children, Severe malnutrition, Retinol, Retinol binding protein, Diarrhoea, ALRI

**Relevance of the protocol:**

Vitamin A deficiency is an important global health problem including Bangladesh. The problem is greater among under-five children, particularly those malnourished. Vitamin A supplementation reduces morbidity from diarrhoeal diseases and also prevents diarrhoea episodes. On the other hand, there are conflicting reports on the role of vitamin A supplementation on morbidity from acute lower respiratory infections (ALRI) including pneumonia; in non-malnourished children supplementation has actually been reported to be associated with increased ALRI incidence and morbidity. The WHO committee (Underwood et al, 1992) has reviewed both the risk and benefit of mega dose (200,000 IU) vitamin A supplementation during acute illness, particularly diarrhoea, irrespective of the nutritional status of under-5 children (IVACG Policy Statement on Vitamin A, Diarrhoea, and Measles. <http://www.ilsi.org/measles.html> at 1500h on 13 July 2005). In Bangladesh high potency (200,000 IU) of vitamin A is routinely supplemented to under-5 children every 6 months. Absorption of vitamin A precursors from the GI tract is reduced in severely malnourished children, who also lack in retinol binding protein (RBP), required for transportation of retinol to target organs. It can thus be assumed that a significant proportion of supplemented vitamin A is excreted in feces and urine of malnourished children. The excretion of vitamin A substantially increases during acute infections including diarrhoeal diseases. On the other hand, free vitamin A, consequence of reduced RBP, increases their concentration in the body increasing the possibility of adverse events including “pseudotumor cerebri”. It has recently been observed that low-dose daily supplementation of vitamin A to malnourished children produces comparable or better effect on recovery from acute illness and also in preventing infectious diseases among under-five children. However, the studies have limitations such as small sample size, delayed assessment of retinol after supplementation, which needs to be addressed in a well-designed clinical trial. We hope that our proposed study will enable us to compare the efficacy of low-dose daily administration of vitamin A with that of initial mega dose followed by daily low dose of vitamin in children presenting with acute diarrhoeal diseases with or without ALRI. If the results of this study indicate that the daily low-dose has similar efficacy to that of the currently recommended mega dose followed by daily dose of vitamin A that would have important programmatic implications.

**Centre’s priority: (as per strategic plan)** Nutrition. Code No. 3

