**Hypothesis to be tested:**

Concisely list in order, in the space provided, the hypothesis to be tested and the Specific Aims of the proposed study. Provide the scientific basis of the hypothesis, critically examining the observations leading to the formulation of the hypothesis.

We hypothesize that a daily low dose (5,000 IU) administration of vitamin A will be more effective than a single high dose (2000,000 IU) followed by daily low doses in the recovery of diarrhoea and pneumonia in severely malnourished hospitalized children, and that it will be safe to use this low-dose schedule.

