There will be two treatment groups: (i) test intervention, and (ii) comparator.

1. Treatment group: Will receive four capsules of vitamin A placebo orally (2 capsules for children aged <12 months) on the day of enrollment plus an oral dose of 5000 IU of vitamin A (in the form of multivitamin drops), and the same oral dose of vitamin A for the next 14 days i.e. throughout their entire nutrition rehabilitation phase in the hospital.
2. Comparator group: Will receive oral mega dose (4 capsules of vitamin A, each containing 50,000 IU i.e. a total of 200,000 IU; 2 capsules for children aged <12 months i.e. a total of 100,000 IU) plus an oral dose of 5000 IU of vitamin A (in the form of multivitamin drops), and the same oral dose of vitamin A for the next 14 days i.e. throughout their entire nutrition rehabilitation phase in the hospital.

A local pharmacutical company (Drug International, Bangladesh) will prepare and supply vitamin A capsules and placebo for the study. One of the investigators will administer the study interventions to the participating children following the randomization schedule at a fixed time of each day, and the date and time of actual administration will be recorded. Randomization will be done by an experienced scientist, not involved in the study in any way, using a block randomization method with variable sizes of blocks between 2 to 6.

Sample size

The sample size of this study has been estimated on expected proportions of clinical success in two groups. Earlier studies have observed 69% and 65% clinical recovery among children suffering from shigellosis and cholera respectively [53, 54], and 60% for pneumonia (personal communication with [name], Kamlapur field site of ICDDR,B) within 48 hours when treated with an effective antimicrobial agent. We assume that the recovery rate would remain same (i.e. 70%) in the high followed by low dose vitamin A group and there would be 15% increase in the rate i.e. 85% in the low dose vitamin A group. Considering 80% power at 5% significance the sample size is estimated as follows:

N = P1 (100-P1) + P2 (100-P2)  F (  ) where P1= 70% and P2 = 85%.

(P1- P2)2

= 118.  = 7.84

Thus the required sample size is 118 in each group, and with an anticipated dropout rate of around 10% the sample size will be 130 children in each of the two treatment groups i.e. a total of 260 children.

Patient recruitment, Clinical and Laboratory Assessments

1. **Patient recruitment**

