**Justifications for conducting this research in human subjects**

Vitamin A deficiency is a major nutritional problem in developing countries including Bangladesh, and under-five children, particularly malnourished children are at higher risk. ALRI/pneumonia and diarrhoea are the two most common illnesses of under-five children. The beneficial role of high dose vitamin A supplementation, as an adjunct therapy in the treatment of diarrhea, has been documented in different studies. However, high dose vitamin A supplementation did not produce any beneficial effect on recovery from ALRI in well-nourished children with adequate stores, rather it increased the incidence of ALRI. WHO estimated that the lives of one million children could be saved globally each year through high dose supplementation of vitamin A. The results of five large trials in Asia have observed 20-30% drops in deaths from diarrhoeal diseases and pneumonia, and about one-third reduction in clinic attendance rate, hospital admissions and morbidity among vitamin A supplemented children. However, other studies have observed higher incidences of adverse events among malnourished children receiving high dose of vitamin A supplementation. The proposed study will examine if daily administration of a low dose of vitamin A produces similar effect on disease morbidity and lesser incidence of adverse events as compared to children receiving high dose vitamin A followed by daily administration of a low dose of vitamin A.

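### The protocol hypothesises, sizes and tests for superiority of the low dose, yet two sections frame the result as similar efficacy, for which it has no margin or interval criterion

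*Protocol*

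**What the plan says.** Three parts of the protocol set up a superiority trial.

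- *Hypothesis to be tested*: "a daily low dose (5,000 IU) administration of vitamin A will be more effective than a single high dose" followed by daily low doses.
- *Sample size*: the comparator is set by "We assume that the recovery rate would remain same (i.e. 70%) in the high followed by low dose vitamin A group", and for the test arm "there would be 15% increase in the rate i.e. 85% in the low dose vitamin A group". The calculation is introduced by "Considering 80% power at 5% significance the sample size is estimated as follows" and gives 118 per group, raised to 130 per group (260 in all) for about 10% dropout.
- *Data Analysis*: t-test, Mann-Whitney, log-rank and Fisher's exact tests, at the 5% level. All are tests of difference.

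Two other parts describe a different question.

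- *Relevance of the protocol*: "If the results of this study indicate that the daily low-dose has similar efficacy to that of the currently recommended mega dose" (followed by daily dosing), this would carry important implications for programmes.
- *Justifications for conducting this research in human subjects*: "The proposed study will examine if daily administration of a low dose of vitamin A produces similar effect on disease morbidity", together with fewer adverse events, compared with the high dose followed by low doses.

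The primary aim is neutral, since it only speaks of comparing proportions. The protocol gives no non-inferiority or equivalence margin and no confidence-interval criterion.

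**The concern.** *More effective* and *similarly effective* are different claims and need different decision rules. A superiority test that reaches significance supports the first. A superiority test that does not reach significance supports neither; it says only that a difference was not shown. To claim similarity, the interval for the difference must exclude a loss judged in advance to matter.

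If the trial ends without a significant difference, a reader who turns to the relevance statement or the ethical justification could take that as the similar result those sections describe. At this sample size a non-significant result is likely even if omitting the initial high dose lowers recovery by an amount that matters. The null result is the case at issue. A significant result in favour of the low dose would be interpretable as planned.

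**Working it through.** **Inputs.** Comparator rate 70%, test rate 85%, 80% power, 5% significance, factor 7.84, 118 per group and 130 with dropout (all *Sample size*). The factor 7.84 = (1.96 + 0.84)² implies a two-sided 5% test. Assumed here, because the protocol gives no figure: true rates other than 85% against 70%, and margins of 10, 15 and 17 points, which are illustrative only.

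**Step 1: reproduce the plan's figure.**
n = [P1(100 − P1) + P2(100 − P2)] × 7.84 / (P1 − P2)² = (2100 + 1275) × 7.84 / 225 = 117.6, so 118 per group. Then 118 × 1.1 = 129.8, so 130. The calculation is sound for superiority. After 10% loss, 130 × 0.9 = 117 evaluable per arm.

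**Step 2: precision if the arms are equal at 70%.**
SE = √(2 × 0.7 × 0.3 / 117) = 0.0599. Half-width = 1.96 × 0.0599 = 0.117, about ±11.7 points. With all 130 per arm, SE = 0.0568 and the half-width is 11.1 points. Equal observed rates would therefore still be compatible with a loss of nearly 12 points, most of the 15-point effect on which the trial is sized.

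**Step 3: chance of a non-significant test when the low dose is truly worse (117 per arm).**

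- 10 points worse (60% against 70%): SE = √((0.21 + 0.24)/117) = 0.0620; Φ(1.96 − 0.10/0.0620) = Φ(0.348) ≈ 0.64.
- 5 points worse (65% against 70%): SE = √((0.21 + 0.2275)/117) = 0.0612; Φ(1.96 − 0.05/0.0612) ≈ 0.87.

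The opposite tail is below 0.3 percentage points in both cases. With all 130 per arm the figures are about 60% and 86%.

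**Step 4: power to show non-inferiority if the arms are equal at 70%.**
Power = Φ(margin/SE − 1.96), with SE = 0.0599.

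| Illustrative margin | margin/SE − 1.96 | Power |
|---|---|---|
| 10 points | −0.29 | 39% |
| 15 points | 0.54 | 71% |
| 17 points | 0.88 | 81% |

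For 80% power the evaluable number per arm is 2 × 0.21 × 7.84 / margin²: 330 for 10 points and 147 for 15 points. The planned size reaches 80% only near a 17-point margin, which is wider than the superiority effect itself.

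**Step 5: why these figures are best case.**
The protocol lists two primary outcomes, resolution of diarrhoea and resolution of ALRI, and *Final inclusion in the study* admits children with either condition or both. A child with only one condition contributes to only one outcome, so each may have fewer than 117 per arm. If, as an assumption, 60 per arm contributed, the half-width would be 1.96 × √(0.42/60) = 16.4 points, and a true 10-point loss would be non-significant about 79% of the time.

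**The case against.** The strongest reply is that the operative design is coherent. Hypothesis, sample size and tests all point to superiority, and a superiority trial needs no margin. Similarity appears as a study aim or use only in the relevance statement and the ethical justification. The first is a single conditional sentence, and the sentence before it speaks only of comparing efficacy. How intervals are reported and interpreted is commonly left to a statistical analysis plan, which is not at hand.

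Much of this stands. The missing interval rule would not be a finding on its own, and the relevance sentence alone would be weak evidence. The ethical justification is harder to set aside: it says outright that the study will examine whether the effect is similar, which conflicts with "will be more effective than a single high dose" in the hypothesis. A later analysis plan could add an interval rule, but it would not by itself remove two conflicting statements of purpose from the protocol.

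Two stronger readings are tempting and are not supported. One is that concluding similarity is the trial's purpose and that the high dose would be abandoned on p > 0.05. No section states such a decision rule or says the high dose would be dropped; the text speaks only of programmatic implications. The other is that non-inferiority followed by superiority can be added at no cost in type I error. That holds within one endpoint whose margin is already fixed. Here there are two primary outcomes and no margin. The protocol's own background also conflicts on whether the high dose helps in diarrhoea, so it offers no clear basis for choosing a margin.

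**Conclusion.** The concern holds as a conflict between statements of purpose, with a definite consequence for a null result. The hypothesis, sample size and analysis section describe superiority; the relevance statement and the ethical justification describe similarity, for which the protocol has no criterion. A non-significant test could be read as similar efficacy, and the design cannot support that. At best the interval is about ±11.7 points, and a true 10-point loss would be missed about 64% of the time.

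These figures assume 117 evaluable children per arm, a 70% comparator rate, one binary endpoint and normal approximations. Fewer children per outcome would make precision worse. The non-inferiority figures depend on the margin, and one of about 17 points or more would be adequately powered at this size, but the protocol states none.

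A reader might infer that the sample size is miscalculated. It is not: 118 per group reproduces for the superiority comparison.

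**What to change.** Reword *Relevance of the protocol* and *Justifications for conducting this research in human subjects* to match the superiority hypothesis. In *Data Analysis*, state that the risk difference with its two-sided 95% confidence interval will be reported for each primary outcome, and that a non-significant test will not be interpreted as similar efficacy.

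If the investigators wish to keep a similarity claim, the protocol must:

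- fix and justify a margin before enrolment, or at the latest before any outcome data are seen;
- name the primary outcome or outcomes it applies to, and how multiplicity across the two is handled;
- allow the claim only if the lower limit of the interval (low dose minus comparator) excludes a loss as large as the margin;
- state the power for that margin at the planned size.

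The core fix costs wording and an interval-reporting rule, with no extra children and no change to treatment. Its downside is that a null result would support a weaker conclusion than those two sections now suggest. Keeping a similarity claim at the present size would mean accepting and stating modest power.

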**Programmes**

Child Health Programme  Health and Family Planning Systems Programme

Nutrition Programme  Population Programme

Programme on Infectious Diseases & Vaccine Science  Reproductive Health Programme

Poverty and Health Programme  HIV/AIDS Programme

**Population: Inclusion of special groups** (*Check all that apply)*:

Gender  Pregnant Women

Male  Fetuses

Female  Prisoners

Age  Destitutes

0 – 5 years  Service providers

5 – 9 years  Cognitively Impaired

10 – 19 years  CSW

20 – 64 years  Others (specify _______________________)

65 +  Animal

**NOTE:** It is the policy of the Centre to include men, women and children in all biomedical and behavioural research projects involving human subjects unless a clear and compelling rationale and justification (e.g. gender specific or inappropriate with respect to the purpose of the research) is there. Justification be provided in case inclusiveness of study participants is not proposed in the study.

**Project / study Site (***Check all the apply)*:

Dhaka Hospital  Mirsarai

Matlab Hospital  Patyia

Matlab DSS area  Other areas in Bangladesh _______________

Matlab non-DSS area  Outside Bangladesh

Mirzapur name of country: ______________________

Dhaka Community  Multi centre trial

Chakaria (Name other countries involved)

Abhoynagar  **______________________________________**

**Type of Study** *(Check all that apply)*:

Case Control study  Cross sectional survey

Community based trial / intervention  Longitudinal Study (cohort or follow-up)

Program Project (Umbrella)  Record Review

Secondary Data Analysis  Prophylactic trial

Clinical Trial (Hospital/Clinic)  Surveillance / monitoring

Family follow-up study  Others

**NOTE:** All clinical studies/trials should be registered in appropriate websites, preferably at [www.clinicaltrials.gov](http://www.clinicaltrials.gov/). When the study is registered in website(s), the PI should provide website address, registration number, and date of registration to the Committee Coordination Secretariat for entering these information into the Centre’s database of your research protocol.

**Targeted Population** *(Check all that apply)*:

No ethnic selection (Bangladeshi)  Expatriates

Bangalee  Immigrants

Tribal groups  Refugee

**Consent Process** *(Check all that apply)*:

Written  Bengali language

Oral  English language

None

**Proposed Sample size: 260** Total sample size: 260

Sub-group: High dose vitamin A-130 Low-dose vitamin A: 130

_______________________________________ ______________________________________

**Determination of Risk: Does the Research Involve** *(Check all that apply)*:

Human exposure to radioactive agents?  Human exposure to infectious agents?

Fetal tissue or abortus?  Investigational new drug

Investigational new device?  Existing data available via public archives/source

(specify________________________)  Pathological or diagnostic clinical specimen only

Existing data available from Co-investigator  Observation of public behavior

New treatment regime

## Yes/No

Is the information recorded in such a manner that subjects can be identified from information provided directly or through identifiers linked to the subjects?

Does the research deal with sensitive aspects of the subject's behaviour; sexual behaviour, alcohol use or illegal conduct such as drug use?

Could the information recorded about the individual if it became known outside of the research:

a. place the subject at risk of criminal or civil liability?

b. damage the subject's financial standing, reputation or employability; social rejection, lead to stigma, divorce etc.

**Do you consider this research** *(Check one)*:

greater than minimal risk  no more than minimal risk

only part of the diagnostic test

Minimal Risk is "a risk where the probability and magnitude of harm or discomfort anticipated in the proposed research are not greater in and of themselves than those ordinarily encountered in daily life or during the performance of routine physical, psychological examinations or tests. For example, the risk of drawing a small amount of blood from a healthy individual for research purposes is no greater than the risk of doing so as a part of routine physical examination".

**PROJECT SUMMARY:** Describe in concise terms, the hypothesis, objectives, and the relevant background of the project. Describe concisely the experimental design and research methods for achieving the objectives. This description will serve as a succinct and precise and accurate description of the proposed research is required. This summary must be understandable and interpretable when removed from the main application. **( TYPE TEXT WITHIN THE SPACE PROVIDED).**

Vitamin A deficiency is a major nutritional problem in many developing countries, including Bangladesh. Globally, an estimated 140-250 million under-five children are deficient of vitamin A and 5 million of them have severe deficiency. Like other micronutrients, malnourished children are also deficient of vitamin A, and frequent common illnesses e.g. diarrhoea, and upper respiratory tract infections including pneumonia in this age group worsens their deficiency states.

The low serum retinol levels in malnourished children perhaps represents a combined effect of lower absorption of vitamin A precursors from their intestine and lack of carrier protein, retinol-binding protein (RBP), which is synthesized in liver and required for carrying retinol to the target organs, leading to development of the features of vitamin A deficiency. In infectious diseases including diarrhoea, excretion of vitamin A is substantially increased in urine and its functions (e.g. integrity of epithelial cells throughout the body)[1] are seriously compromised at tissue levels.

Acute lower respiratory tract infections (ALRI) including pneumonia, and diarrhoeal diseases are the two commonest diseases that affect under-five children. The beneficial role of high-dose vitamin A supplementation, as an adjunct to treatment of diarrhoea, has been documented in several studies. However, high dose vitamin A does not provide any benefit in the management of ALRI in well-nourished children with adequate vitamin A stores, and in fact, has been associated with increased incidence of ALRI. Some studies have observed increased incidence of diarrhoea and symptomatic respiratory infections after 2 weeks of receiving high dose of vitamin A. One study failed to observe any difference in the mortality (8% vs. 8.4%) and duration of hospitalization (10 days vs. 9 days) between groups of children receiving a high and a low dose of vitamin A. In a subgroup analysis, mortality was lesser in the group of children who received daily low dose compared to those who received single high dose (9.7% vs. 11.1%), and the reduction in deaths was more pronounced in children who had oedematous malnutrition on admission. Results of these two studies, indicating higher deaths in moderately malnourished and oedematous children receiving high dose vitamin A, need to be further examined in a well-designed study because of its implications on vitamin A supplementation programmes.

With the above background, we propose a study to examine the effects of daily low dose vitamin A (5000 IU for 15 days) in severely malnourished children, aged 6-59 months, with diarrhoea, with or without pneumonia, and compare that with initial high dose (200,000 IU) followed by a daily low doses (5000 IU for 14 days) of vitamin A in a randomized, controlled clinical trial. All children enrolled in the study would receive the standard care and treatment for their diarrhoea and associated illnesses. Serum concentrations of retinol and retinol binding protein will be measured in study children before randomization, after 48 hours (i.e. on 3rd day) and 14 days later (i.e. on 15th day). The duration of diarrhoea, and proportion of children recovering from pneumonia (return of respiratory rate to normal, and resolution of fever, and ability to eat and drink well) within 48 hours will be the primary outcome measures, and the findings would be correlated with serum retinol and retinol binding protein. We hope that this study might provide valuable information in defining an evidence-based programme for vitamin A supplementation to severely malnourished children.

DESCRIPTION OF THE RESEARCH PROJECT

